## Methods: participants, interventions and outcomes

### Study setting {9}

The study will take place in villages in Saraya district, Senegal. Saraya district borders Mali to the east and Guinea to the south and is composed of the rural communities of Sabadola, Khossanto, Bembou, Missirah Dantilla, Missirah Sirimana and Medina Baffe and includes 102 villages occupying a land area of 7803 km^2^, with an estimated total population of 61,756 people, including 10, 566 under-five children and 5,770 children aged between 5 and 10 years. The Saraya department has one health centre, 10 health posts, two health huts and 39 home care providers (2019 population census estimate) (Fig. 1). Over 70% of the population live more than 15 km from a health facility. The main ethnic groups are Malinke and Diakhanke. The climate is Sudano-Sahelian with two seasons, a dry season from November to May and a rainy season from May to November. The average rainfall ranges from 16 to 4mm during these months, with an average rainfall of 213 mm during the peak period in August. Mean daily temperatures range from 14 to 36°C from July to February and 21–40°C from March to June [17]. Saraya district is one of the zones in Senegal most affected by both malaria [18] and helminths [19].

### Eligibility criteria {10}

#### Inclusion criteria

Male or female children aged 1–14 yearsProvision of written informed consent by the parent/caregiver and a positive assent by children aged ≥ 12 years (in line with legal regulations in Senegal)Willingness to provide finger-prick blood samples and urine and stool samplesResidence in the study area for at least six months

#### Exclusion criteria

Acutely ill child at the time of the drug administrationA child whose parents/caregivers decline to provide consentA known HIV-positive child receiving cotrimoxazole prophylaxisA child who has received a dose of either sulphadoxine-pyrimethamine (SP), amodiaquine (AQ), albendazole (ALB) or praziquantel (PZQ) during the previous six  monthsA child with a known allergy to any of SP, AQ, ALB or PZQ

### Who will take informed consent? {26a}

Written informed consent will be obtained from potential trial participants by a trained research assistant. The Participant Information Sheet will be translated to French and a trained field assistant who is a native speaker will interpret the information in a Senegalese language preferred by the parents/caregivers. If the parent/caregiver is not able to read and write in French, a literate adult witness will be present throughout the whole consent process and sign and date the consent form. A parent/caregiver must provide written informed consent form, before a child aged <12 years is enrolled into the study. For children aged ≥ 12 years, positive assent is required in addition to the parental consent.

### Additional consent provisions for the collection and use of participant data and biological specimens {26b}

Additional consent provisions for the collection and use of participant data and biological specimens in future studies will be obtained by a trained research assistant during the consent discussion.

### Interventions

#### Explanation for the choice of comparators {6b}

To ensure objectivity in the reporting of adverse events among the study children, vitamin A and a zinc supplement will be used as controls, so that all children randomised to each study arm receive three drugs [20, 21]. Vitamin A will be an oral liquid, oil-based preparation of retinyl palmitate or retinyl acetate, obtained from the UNICEF, Senegal office. The zinc preparation will be a citrus-flavoured tablet containing 25 mg Zn in the form of zinc sulfate and will be obtained from Biolectra Zink; Hermes Arzneimittel GmbH, Munich, Germany. To minimise under- and over-dosing while keeping simple dosage recommendations, the doses of vitamin A and zinc supplement will be based on the child’s age, as follows: children aged 1–14 years will receive 200,000 IU vitamin A and zinc (40 mg/kg) and zinc supplement (40mg/kg) based on their body weight.

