**PZQ tablet (40 mg/kg)**	
• Children aged 1–14 years will receive praziquantel based on their body weight 40mg/kg	

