### Strategies to improve adherence to interventions {11c}

Given that the side effects caused by interactions of praziquantel with albendazole are dose-dependent [22, 23] and can be reduced by taking praziquantel with carbohydrate meals [24], we will give praziquantel to the study children based on the dose recommended by WHO (40mg/kg) and we will ensure that the children take a carbohydrate-rich meal before administration of the drugs. A trained member of the research team will visit the children at home to administer the drugs in the presence of their parents/caregivers. Children who start treatment but who could not be found at home after reasonable efforts will be excluded from the study. A simple, user-friendly recording tool will be used to capture the drug administration for each child.

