### Data collection and management

#### Plans for assessment and collection of outcomes {18a}

On the start day of the study, the research staff will confirm the parent/caregiver’s willingness to allow their child’s continued participation in the study and administer a purpose-designed electronic questionnaire to the parents/caregivers. The questionnaire will cover information such as socio-demographic, health and residence characteristics, history of de-worming and prior malaria treatment. Height/length (cm) and weight (kg) of each child will be measured and anthropometric indices, height-for-age, weight-for-age, weight-for-height and body mass index, will be calculated using the WHO AnthroPlus software (www.who.int/growthref/tools/en/). The study villages will be mapped by recording each study participant’s household global positioning system (GPS) coordinates with a hand-held GPS device.

The quantitative study will be implemented in collaboration with the SMC and NTD providers during the SMC campaign which will start in Saraya district by the middle of June 2022. Two hundred children pre-school and school-age children will be enrolled into each arm of the study as described above. The study procedures are illustrated in Fig. 2 and Table 2. The children will be evaluated one  month after the last course of SMC cycles at the end of malaria transmission season to measure haemoglobin concentration and to obtain a further blood film, dried blood spot, stool and urine samples.

**Table 2 Tab2:** Schematic diagram of the study procedures

SMC cycle	1					2, 3 and 4	End of malaria season
Timelines (days)	Day 0–1	Day 0	Day 1	Days 2 and 3	Days 4–6		
**Study procedures**						**Passive surveillance**	
Informed consent ± assent	X						
Enrolment and questionnaire administration to parent/caregivers		X					
Distribution of collecting bottles for stool sample	X						
Sample collection (finger-prick blood, urine, stool)		X					
**Randomisation**		X					
Group 1: vitamin A + zinc		X	AQ + SP	AQ			
Group 2: PZQ + vitamin A		X	AQ + SP	AQ			
Group 3: ALB + PZQ		X	AQ + SP	AQ			
Safety assessments		X	X	X	X		
**Post-intervention survey**							X
Sample collection: finger-prick							X
Sample collection: stool							X
Sample collection: urine							X

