### Trial status

This paper is based on protocol version 2.0, dated 8 April 2022. Recruitment of the study participants will coincide with the commencement of the first cycle of SMC scheduled by the Senegal Ministry of Health for 17 June 2022. The recruitment was completed on 21 June 2022, and the follow-up of the enrolled participants will continue until 30 November 2022.

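### The control arm's zinc dose is printed as 40 mg/kg, which cannot be right for a 25 mg tablet, and the article gives no other zinc dose

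*Protocol article*

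**What the plan says.** All the zinc dosing information is in the section Explanation for the choice of comparators {6b} of the protocol article. The product is a "citrus-flavoured tablet containing 25 mg Zn in the form of zinc sulfate". The dosing rule opens by saying that "the doses of vitamin A and zinc supplement will be based on the" child's age, with the stated aims of avoiding under- and over-dosing and keeping the recommendations simple. The same sentence then gives the dose for children aged 1–14 years as "200,000 IU vitamin A and zinc (40 mg/kg) and zinc supplement (40mg/kg) based on their body weight".

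The same mg/kg figure appears for praziquantel. Table 1 reads "Children aged 1–14 years will receive praziquantel based on their body weight 40mg/kg", and the section on adherence strategies {11c} repeats 40 mg/kg for praziquantel as the WHO-recommended dose.

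Zinc is allocated to one arm only. The row in Table 2 is "Group 1: vitamin A + zinc", given on Day 0. Group 2 receives praziquantel with vitamin A, and Group 3 receives albendazole with praziquantel.

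**The concern.** The dosing sentence has three faults. It states zinc twice. It changes the basis from age to body weight. It gives an amount that does not fit the tablet named shortly before it.

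The trial is described as a non-inferiority comparison of side effects, with adverse events as the primary outcome and Group 1 as the SMC-alone comparator. The control regimen is therefore part of the primary contrast. As printed, a reader cannot tell how much zinc the control children received, cannot reproduce the regimen, and cannot judge the article's statement (section Control) that vitamin A and zinc have not been shown to affect the outcomes.

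There is also a conditional risk. If staff followed the text literally, Group 1 would be overdosed. Its adverse-event rate could rise, and that would bias the comparison towards finding the combinations no worse than SMC alone. If a small intended dose was given, this wording causes no bias.

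**Working it through.** **Inputs from the document**
- Zinc dose as written: 40 mg/kg by body weight ({6b}).
- Tablet strength: 25 mg Zn ({6b}).
- Age range: 1–14 years (Eligibility criteria {10}).

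**Assumption.** The article gives no body weights. I use 10, 20 and 30 kg as illustrations, and 8 to 50 kg as a wide range for these ages.

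**Step 1: the dose as written.** Dose = 40 mg/kg × weight; tablets = dose / 25 mg.

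| Assumed weight (kg) | Dose (mg) | 25 mg tablets | One tablet (mg/kg) | Written dose ÷ one tablet |
|---|---|---|---|---|
| 8 | 320 | 12.8 | 3.125 | 12.8 |
| 10 | 400 | 16 | 2.5 | 16 |
| 20 | 800 | 32 | 1.25 | 32 |
| 30 | 1,200 | 48 | 0.83 | 48 |
| 50 | 2,000 | 80 | 0.5 | 80 |

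**Step 2: the weight at which one tablet fits.** 25 mg / 40 mg/kg = 0.625 kg, far below the weight of any child aged 1–14 years.

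**Step 3: can another reading rescue the figure?**
- *A flat 40 mg, treating the per-kilogram unit as the slip:* 40 / 25 = 1.6 tablets, which is not a practical tablet dose.
- *40 mg/kg as weight of zinc sulfate monohydrate* (zinc fraction 65.38 / 179.45, about 36%, from molar masses): 4.7 tablets at 8 kg and 29.1 at 50 kg. One tablet fits only at about 1.7 kg.
- *40 mg/kg as weight of zinc sulfate heptahydrate* (65.38 / 287.55, about 23%): 2.9 tablets at 8 kg and 18.2 at 50 kg. One tablet fits only at about 2.7 kg.

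No reading gives a single control tablet or a simple age-based dose.

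**Step 4: is the intended dose given elsewhere?**
- Fig. 2 legend: zinc named for the first group, no dose.
- Table 1: rows for SP, AQ, ALB and PZQ only.
- Control section: zinc named, no dose.
- Adherence section {11c}: praziquantel dose only.
- Table 2: zinc on Day 0 for Group 1, no dose.

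The sentence in {6b} is thus the only zinc dosing rule in the article, and the intended dose cannot be recovered from it. The match with the praziquantel wording suggests where the figure came from, but that is an inference.

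**The case against.** The strongest reply is that this is a drafting slip with no demonstrated consequence. The document itself makes the literal reading implausible. It names a 25 mg tablet, aims to avoid over-dosing, wants simple dosing, and uses the controls to equalise the number of drugs across arms. Handing a child 16 to 48 tablets would defeat all of that, and trained staff give the drugs. The tablet counts show that the number is impossible; they do not measure harm to the trial. The vitamin A dose, the zinc product, the arm and the day are all clear, so only the amount of zinc is in doubt. The article condenses a full protocol (version 2.0) that is not shown and may state the dose correctly. The drug recording tool may not capture milligrams or tablet counts.

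Most of this stands. A slip is the likely cause, it was not a deliberate design decision, the bias is hypothetical, and the trial's operating documents may well hold a sensible dose. None of it rescues the printed figure. The objection is not that the article leaves the dose out; it prints a dose and prints it wrongly. A reader can see the error but cannot correct it. The limit on the recording tool is a fair caution about how much the record check will recover.

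**Conclusion.** The concern holds. The zinc dose as printed is wrong: it contradicts its own stated age basis, duplicates itself, and exceeds one tablet by 16, 32 and 48 times at assumed weights of 10, 20 and 30 kg. That conclusion depends on the assumed weights only for the exact multiples, since no child in the age range could weigh 0.625 kg.

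The consequence for the trial is uncertain. Nothing shows that 40 mg/kg was given, and the effect on the adverse-event comparison cannot be estimated from the document. What is certain is that the comparator regimen for the primary safety outcome cannot be reproduced from this text. It should be fixed: the error is clear, the effect is unknown and correction is cheap.

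**What to change.** Replace the 40 mg/kg zinc wording, including its repetition, with one zinc dose in milligrams or whole 25 mg tablets, set out by age band if dosing is by age.

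The Trial status section states "The recruitment was completed on 21 June 2022", so the correction cannot change what was given. The adherence section {11c} says a "recording tool will be used to capture the drug administration for each child"; use those Day 0 records to establish what Group 1 received, and report that dose with the results. If the tool did not record quantities, say so and give the dose in the instructions that staff worked from. Notify the safety monitor and the ethics committees only if the records show that the written dose, or another unintended dose, was given.

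The cost is one corrected sentence and a check of existing records for roughly 200 children. Design, sample size and analysis are unchanged.

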#### Intervention description {11a}

Given that this study will be implemented during SMC campaign and in collaboration with the SMC programme of the Senegal Ministry of Health, the SMC drugs: AQ and SP will be obtained from the SMC implementation unit of the Ministry. The albendazole [ALB] and praziquantel [PZQ] needed for this study will be procured from GlaxoSmithKline and Merck, respectively. The doses of SP and AQ for SMC and anthelminthic drugs will be based on the child’s age in Table 1.

**Table 1 Tab1:** Dosages of SMC and anthelminthic drugs to be used in this study

**SP tablet (500mg + 25mg)**	
• Children aged 12–59 months will receive a full tablet as a single dose on the first day	
• Children aged 5–10 years will receive one and a half tablet as a single dose on the first day	
• Children aged 11–14 years will receive two tablets as a single dose on the first day	
**AQ tablet (153mg base)**	
• Children aged 12–59 months will receive a full tablet as a single daily dose for 3 consecutive days	
• Children aged 5–10 years will receive one and a half tablet as a single dose for 3 consecutive days	
• Children aged 11–14 years will receive two tablets as a single dose for 3 consecutive days	
**ALB tablet (200 or 400 mg depending on age)**	
• Children aged 12–24 months will receive a half dose of albendazole 200mg	
• Children aged greater than 2 years and up to 14 years will receive a single dose of albendazole 400mg	
**PZQ tablet (40 mg/kg)**	
• Children aged 1–14 years will receive praziquantel based on their body weight 40mg/kg	

#### Control

To ensure objectivity in the reporting of adverse events among the study children, vitamin A and zinc supplement will be used as control drugs, so that the children randomised to all study arms receive three drugs. Vitamin A and zinc supplements have not been shown to affect the outcomes of this study [20, 21].

#### Criteria for discontinuing or modifying allocated interventions {11b}

There will be no special criteria for discontinuing or modifying allocated interventions.

### Strategies to improve adherence to interventions {11c}

Given that the side effects caused by interactions of praziquantel with albendazole are dose-dependent [22, 23] and can be reduced by taking praziquantel with carbohydrate meals [24], we will give praziquantel to the study children based on the dose recommended by WHO (40mg/kg) and we will ensure that the children take a carbohydrate-rich meal before administration of the drugs. A trained member of the research team will visit the children at home to administer the drugs in the presence of their parents/caregivers. Children who start treatment but who could not be found at home after reasonable efforts will be excluded from the study. A simple, user-friendly recording tool will be used to capture the drug administration for each child.

### Relevant concomitant care permitted or prohibited during the trial {11d}

Implementing the concurrent administration of SMC and anthelminthic medications in this trial will not require alteration to the usual care pathways (including use of any medication) and these will continue for all trial arms.

#### Provisions for post-trial care {30}

There is no anticipated harm and compensation for trial participation.

### Outcomes {12}

#### Primary outcome

All solicited and unsolicited adverse events will be assessed for causal relationships to the study medications, for six consecutive days after the administration of anthelminthic drugs.

#### Secondary outcomes

Prevalence and intensity of *Plasmodium*-helminth co-infectionFaecal egg counts for each of the four parasites (hookworm, *A. lumbricoides*, *T. trichiura*, *and S. mansoni*) and urine egg count for *S. haematobium* will be recorded, and the prevalence and arithmetic mean intensity of *Plasmodium* infection will be calculated before and after concurrent administration of SMC and anthelminthic drugs (i.e. at the end of malaria transmission season).Prevalence of anaemia and mean haemoglobin concentrationHaemoglobin concentration of all children will be checked using a HemoCue® haemoglobin analyser, before and after co-administration of SMC and anthelminthic drugs (i.e. at the end of malaria transmission season).

### Participant timeline {13}

#### Sample size {14}

Haemoglobin (Hb) concentration was used to calculate the sample size. Given that the mean Hb concentration in the SMC alone group in a previous study [18] in the same population was 10.5 g/dl, we assumed a mean Hb concentration of 11.0 g/dl in the SMC + anthelminth arm and a SD of the Hb concentration of 1.5 g/dl. To detect a mean difference between the treatment arms of 0.5 g/dl with 90% power at a 95% level of statistical significance, a minimum of 189 children per treatment arm will be needed. Allowing for 10% loss to follow-up, approximately 200 children will be enrolled into each treatment arm.

Based on a recent survey conducted in the study site (unpublished data), we assumed that the prevalence of any malaria or helminth infection in the SMC group will be 30%, the prevalence of any malaria or helminth infection in the SMC + anthelminth arms will be 16% and the relative risk will be 0.53 (that is, 47% reduction in the SMC + anthelminth arms compared to the SMC alone group). A minimum sample size of 188 children was considered sufficient to give 90% power at 95% confidence interval and 5% level of precision. Adding 10% loss to follow-up, approximately 200 children will be needed for each treatment arm. Therefore, a total of 600 children aged 1–14 years will be enrolled and randomly assigned at a ratio of 1:1:1 into the control and the two intervention arms.

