### Statistical methods

#### Statistical methods for primary and secondary outcomes {20a}

Infection intensities of positive samples will be calculated as the geometric mean of parasites per microlitre of blood for and geometric mean of eggs per gram of faeces for *S. mansoni*. For *S. haematobium*, infection intensity will be calculated as geometric mean of eggs per 10ml of urine. For pre- and post-intervention time points, the chi-square test will be used to compare proportions (prevalence) of malaria infection and prevalence of anaemia between the intervention and control groups. Similarly, for each time point, the Student *t*-test will be used to compare geometric mean parasite counts and mean haemoglobin concentrations between the intervention and control groups. The repeated measures analysis of variance will be used to compare geometric mean parasite counts and mean haemoglobin concentrations where repeated measurements for pre- and post-intervention time points are compared. All statistical tests will be two-sided at a significance of alpha < 0.05.

Qualitative data will be managed by NVivo software version 12.0 and analysis will be done by initially coding the main themes that emerge from the transcribed texts. The themes will subsequently be sorted and collated into categories and sub-categories. Hypotheses and concepts will be developed inductively from the themes. The findings of the qualitative and quantitative data addressing similar concepts will be triangulated in the final report.

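### Enrolling 200 per arm does not cover the stated 10% loss on 189 or 188 evaluable children, so power at that loss is about 88%, not 90%

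*Protocol article*

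**What the plan says.** Under Sample size {14} the protocol article makes two calculations.

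- **Haemoglobin.** The control mean comes from earlier work: "the mean Hb concentration in the SMC alone group in a previous study [18] in the same population was 10.5 g/dl". For the intervention, "we assumed a mean Hb concentration of 11.0 g/dl in the SMC + anthelminth arm and a SD of the Hb concentration of 1.5 g/dl". The target is set as "To detect a mean difference between the treatment arms of 0.5 g/dl with 90% power at a 95% level of statistical significance", and the result is that "a minimum of 189 children per treatment arm will be needed". The text continues: "Allowing for 10% loss to follow-up, approximately 200 children will be enrolled into each treatment arm".
- **Any malaria or helminth infection.** Prevalence is taken as 30% on SMC alone and 16% with anthelminthics. The minimum is 188 per arm, again for 90% power. The text continues: "Adding 10% loss to follow-up, approximately 200 children will be needed for each treatment arm".

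The total is then fixed at 600, allocated 1:1:1. On the test level, Statistical methods {20a} says: "All statistical tests will be two-sided at a significance of alpha < 0.05". Section {20c} leaves children with data at only one of the two time points out of the full analysis set.

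**The concern.** Both calculations start from a number that must be evaluable, state a 10% attrition rate, and arrive at 200. A 10% allowance on 189 or 188 should end near 210. The figure of 200 adds only 11 or 12 children, about 6%.

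The attrition allowance matters for these endpoints. The second measurement is taken at the end of the transmission season, one month after the last SMC course, and {20c} removes children who lack it from the full analysis set. Every child lost therefore reduces the analysed number. If the loss is what the plan itself expects, the analysed number falls below both stated minimums and the claimed 90% power is not reached.

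**Working it through.** **Inputs.** From {14}: haemoglobin difference 11.0 − 10.5 = 0.5 g/dl, SD 1.5 g/dl; prevalence 30% and 16%; power 90%; loss 10%; 200 enrolled per arm. From {20a}: two-sided alpha 0.05. Hence z = 1.960 and 1.2816, sum 3.2415.

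**Step 1. Reproduce the stated minimums.**

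- Means: n = 2 × (3.2415 × 1.5/0.5)² = 189.1 per arm. The plan says 189. (The t-test version needs 190.1.)
- Proportions, pooled variance under the null, no continuity correction, mean prevalence 0.23: n = [1.960 × √(2 × 0.23 × 0.77) + 1.2816 × √(0.30 × 0.70 + 0.16 × 0.84)]² / 0.14² = 187.8 per arm. The plan says 188.

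Both minimums reproduce. One-sided tests would need only 155 and 153, so the two-sided 5% reading is the one the plan used.

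**Step 2. Inflate for 10% loss.**

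| | Minimum | n / 0.9 | n × 1.1 | Plan |
|---|---|---|---|---|
| Haemoglobin | 189 | 210 | 207.9 → 208 | 200 |
| Prevalence | 188 | 208.9 → 209 | 206.8 → 207 | 200 |

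Neither formula gives 200.

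**Step 3. What 200 leaves.** 200 × 0.9 = 180 per arm. That is 189 − 180 = 9 short for haemoglobin and 188 − 180 = 8 short for prevalence.

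**Step 4. Power at 180 per arm.**

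- Haemoglobin, normal approximation: 0.5 / (1.5 × √(2/180)) = 3.162; 3.162 − 1.960 = 1.202; power 88.5%. By the noncentral t, 88.4%.
- Prevalence: (0.14 − 1.960 × √(2 × 0.23 × 0.77/180)) / √(0.3444/180) = (0.14 − 0.0869)/0.0437 = 1.213; power 88.7%.

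The haemoglobin difference detectable with 90% power at 180 per arm is 3.2415 × 1.5 × √(2/180) = 0.513 g/dl, against the planned 0.5.

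With no loss at all, 200 per arm gives 91.4% (t-test) and 91.7%.

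**Step 5. Loss that 200 per arm can absorb at 90% power.**

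- Haemoglobin: 1 − 189.1/200 = 5.4% (with the t-test requirement, 1 − 190.1/200 = 4.9%).
- Prevalence: 1 − 187.8/200 = 6.1%.

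Haemoglobin is the binding calculation, at about 5%.

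**The case against.** The strongest reply is that the shortfall hardly matters. Power drops by 1.3 to 1.6 percentage points, the detectable haemoglobin difference moves from 0.50 to 0.513 g/dl, and the 90% figure fails only if loss goes above about 5%. Haemoglobin and infection prevalence are secondary outcomes. The primary outcome is adverse events over six days, which these calculations do not size. The Discussion already concedes that measuring efficacy will probably take a larger study. The text also says only that 200 is approximate.

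Most of this stands as a statement about size. The effect is minor, and nothing here suggests that the trial is compromised. It does not make the sentence correct. The gap between 200 and 210 is 5%, too wide for approximation to explain, and the same slip occurs in both calculations, so neither supports the other. The total of 600 is fixed from it, and no other part of the article repairs it.

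A second objection concerns recovering power by adjusting for baseline haemoglobin. That gain depends on a pre/post correlation the article does not give, and on an analysis of covariance that {20a} does not name. It also does nothing for the prevalence comparison, which is planned as a chi-square test. These limits are real, so baseline adjustment is at most an option for haemoglobin and cannot replace the correction.

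**Conclusion.** The concern holds. The minimums of 189 and 188 are correct, but 200 per arm covers a loss of about 5% to 6%, not 10%. At the plan's own 10% loss, 180 children per arm remain and power is 88.4% for haemoglobin and 88.7% for prevalence, against 90% claimed. It is a small, certain arithmetic error in secondary-outcome calculations, worth correcting because they are the only sample-size justification the article gives.

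The power figures assume the plan's own effect sizes and SD, a pairwise two-sided 5% test with no adjustment for having two intervention arms, loss equal across arms, and, for prevalence, the pooled test without continuity correction that reproduces 188.

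**What to change.** Replace the attrition statement in both paragraphs of {14}. Suggested content: 200 per arm gives about 88% power with 10% loss (180 evaluable), or 90% if loss is no more than about 5%.

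Covering 10% loss in full would have taken 210 per arm, 630 in total. The Trial status section reports that recruitment finished on 21 June 2022, so restating the claim is the practical course. The cost is one slightly less favourable figure.

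Optionally, the haemoglobin comparison could be adjusted for the baseline value, which is already collected. Under analysis of covariance, 189.1 × (1 − ρ²) ≤ 180 requires a pre/post correlation ρ of at least √(1 − 180/189.1) = 0.22 to regain 90% power at 180 per arm. If the comparison is instead the group-by-time test of the planned repeated-measures ANOVA, which for two time points amounts to comparing change scores, 189.1 × 2(1 − ρ) ≤ 180 requires ρ of at least 0.52. The article gives no value for ρ, so any such claim should state the assumed correlation, and the 88.7% for prevalence would still stand.
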